### Digital Health Application (Chorus) and Approach

The FCFN intervention incorporates digital health technology grounded in participatory informatics (using the secure web-based Chorus platform [Chorus Innovations, Inc], which involved end users and navigators in app codevelopment as an inherent and critical component of successful navigation [38]). Chorus is an established digital health platform that provides the basis for a web application named Fostering Connections, which is accessible to a broad range of people (similar to visually creating slides in Microsoft PowerPoint) and includes interactive messaging and mobile web app capabilities [38]. Fostering Connections was adapted based on feedback from CWI families and stakeholders and is designed to support the navigation process across multiple dimensions by (1) supporting bidirectional SMS text messaging (and shared dashboards) to enhance communication between navigators and families, (2) including reminders for upcoming session and behavioral health services appointments, (3) storing navigation documents and resources, and (4) including surveys for completion by navigators. Thus, it is a proven and reliable system that will allow navigators to effectively opt in as well as communicate with, and engage, participants and other providers; in addition, it can be developed and tailored according to research study needs.

### Hypotheses

We hypothesize that youth receiving the FCFN intervention will have increased rates of mental health treatment initiation and engagement compared with youth receiving standard of care. We will also explore hypothesized mechanisms of intervention impact (eg, navigator satisfaction, youth treatment motivation, and perceived barriers to care) as well as potential moderators (eg, sex, race, ethnicity, and out-of-home placement status).

## Methods

### Study Design

Up to 5 FCFNs and 80 families (caregiver-youth dyads) will participate in the RCT to assess the preliminary impact of the FCFN intervention on mental health services use. CWI youth (in in-home or out-of-home placement) aged between 12 and 17 years as well as their caregivers will be referred for study participation at the point of referral from the child welfare system to a partnering mental health clinic (hereinafter referred to as the foster care mental health [FCMH] clinic) that specializes in serving foster care youth by linking them to specialty mental health services. Enrolled families will be randomized to either the FCFN intervention or standard of care. Enrolled CWI youth and their caregivers will complete a computerized set of questionnaires (on a tablet device, mobile phone, PC, or laptop computer) at baseline, midintervention (1-month after baseline), and at 3 and 6 months after randomization.

The trial has been registered with ClinicalTrials.gov (NCT04506437).

### Intervention Condition (FCFN)

Families (n=40) who are randomized to the FCFN intervention will complete six 60-minute intervention sessions in the first 2 to 3 months of the 6-month period. Sessions can be scheduled on a weekly or biweekly basis. The 6 sessions, described in Figure 2, are as follows: *Introduction to the navigator and navigation services*, *Specialty mental health services orientation*, *Clinical care team mapping*, *Barriers to care and stress management*, *Therapy expectations and stigma*, and *Values and motivation to engage in treatment*. The 6-month intervention period also includes brief check-ins with youth and caregivers, typically conducted through the Fostering Connections web application, by telephone and videoconferencing, depending on the preference and availability of families. The 6 intervention sessions will be audio recorded to separately assess for FCFN intervention fidelity by trained study staff (raters).

**Figure 2 figure2:**
[figure not shown]
Session-by-session content.

### Standard of Care (Clinical Case Management Services) Condition

Families (n=40) who are randomized to standard of care (comparison condition) will receive clinical case management services *as usual*, delivered by FCMH clinic case managers. The role of FCMH clinic case managers is to identify mental health treatment referral resources in the community that match current youth mental health service needs. FCMH clinic case managers facilitate direct referral to a community provider and then provide this information for the family to link to community-based care. FCMH clinic case managers do not typically meet with youth and their families directly but rather follow the existing FCMH clinic protocol of facilitating referrals and linkage via telephone and other communication with youth and their families and their FCMH clinic screening clinician.

### Participants

#### FCMH Clinic Study Sample

Recruitment for the study commenced in August 2020 and will conclude by March 2024. Historically, the FCMH clinic has served an annual average of 100 unduplicated youth aged 12 to 17 years with mental health screening and other related services for those with medical necessity. The average length of time in the court dependency process is 6 months, but can be as long as 12 months in cases of family reunification, and up to 18 months in cases of permanency planning or transition-age youth. Youth who reach the age of 18 years while receiving FCMH services are eligible for, and continue to receive, services without disruption.

#### Racial, Ethnic, and Sex Considerations

FCMH clinic data from the 2017-2018 period suggest that the ethnic representation of youth will be approximately 29% Hispanic or Latinx and that the racial representation will be 29% African American, 3% American Indian or Alaska Native, 18% Asian or Pacific Islander, 14% European-American or White, 3% multiethnic, and 4% other. Of the FCMH clinic adolescent caseload, male adolescents represent approximately 41%, and female adolescents represent approximately 59%. African American and Latinx youth are disproportionately represented, given that, of the total population in the clinic’s surrounding area, African Americans comprise only 6.1% and Latinx only 15.1%.

#### Behavioral Health Considerations

On the basis of FCMH clinic data from the 2017-2018 period, medical records identified the primary disorder diagnosis as 43% adjustment, 24% mood, 22% anxiety (including posttraumatic stress disorder [PTSD]), 7% behavioral (eg, oppositional), 1% psychosis, and 3% deferred.

#### Inclusion and Exclusion Criteria

Eligible participants will be youth aged between 12 and 17 years who have an active dependency petition with the local unified family court (newly filed or existing when the RCT commences), are referred to the FCMH clinic for services, have an involved caregiver or legal guardian who can consent and participate in the intervention, and whose family has mobile phone access. The exclusion criteria include youth and caregivers who are monolingual in languages other than English or Spanish, caregiver impairment that would preclude providing informed consent, and the lack of an available guardian for consent.

#### Recruitment and Consent

Study staff will be embedded in the FCMH clinic setting to introduce the study and procedures to eligible families at the time that families meet with FCMH clinic staff (eg, to complete the mental health screening). FCMH clinic staff will refer eligible families to meet with study staff. Interested youth and families will be separately assented or consented in a private place (FCMH clinic staff will not be involved). We will obtain a waiver of parental consent for referred youth.

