### Study Objectives

This study will be the first to develop and test a foster care family navigator (FCFN) intervention for CWI youth that has the potential to significantly improve adolescent mental health disparities, particularly for racial and ethnic minoritized youth. The primary goal of the study is to assess the feasibility, acceptability, and preliminary impact of the FCFN intervention on the mental health services cascade of care (eg, screening, assessment, and treatment initiation) outcomes. Using a randomized controlled trial (RCT) design, we will randomize 80 families to receive either the FCFN intervention or standard of care (clinical case management services): 40 (50%) to FCFN and 40 (50%) to control. Qualitative exit interviews will inform the feasibility and acceptability of the services received during the 6-month period. Primary trial outcomes are mental health treatment initiation and engagement. Other pre- and postservice outcomes, such as proportion screened and time to screening, will also be evaluated.

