#### Randomization

Participants will be randomized (using a computer-generated randomization tool) to either the FCFN intervention group (40/80, 50%) or the standard of care group (40/80, 50%) directly after consent and completion of the baseline assessment.

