**Identification (percentage of court cohort aged 12-17 years; electronic medical record [EMR])**
Percentage screened (Child and Adolescent Needs and Strengths [CANS; short form]), percentage assessed (CANS), and percentage in needTime to screening, full assessment, and determination of need (number of days)

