##### Cascade Outcomes

GLMM analyses of dichotomous outcomes (screening, treatment initiation, etc) will include intervention (FCFN group vs control group) as a fixed between-participants effect. Cox regression analysis (PROC PHREG) will be used to compare the interventions on time-to-event outcomes (eg, time to assessment) using a shared frailty model that accounts for clustering within pods. The potential mediators and mechanisms of change, measured longitudinally (at baseline and at 1, 3, and 6 months) only for FCFN intervention participants, will be initially examined for intervention impact using GLMMs that include a repeated within-participants time effect. The majority of the mediators are scaled variables, anticipated to have normal distributions, but final models and link functions will be chosen based on observed distributions. It will not be possible to test mediation without data from the control group. Therefore, we will identify potential mediators to be studied in the future trial by first determining which potential mediators change between baseline and month 1 or month 3 and then examining whether month 1 or month 3 values and changes between baseline and month 1 or month 3 are associated with cascade outcomes.

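### Screening outcomes are compared between arms although youth can be recruited at the screening visit and randomised after it, so an unknown share of these events precedes allocation

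*Protocol article*

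**What the plan says.** **Recruitment and allocation.** Recruitment and Consent has study staff approach families "at the time that families meet with FCMH clinic staff (eg, to complete the mental health screening"); the screening visit is the only example given. Under Randomization, allocation takes place "directly after consent and completion of the baseline assessment". Study Design describes the entry point differently: youth and caregivers "will be referred for study participation at the point of referral from the child welfare system to a partnering mental health clinic".

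**Eligibility.** Inclusion and Exclusion Criteria admit both new and existing dependency petitions. No criterion requires that the youth is still unscreened or unassessed.

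**Outcomes.** Study Objectives names treatment initiation and engagement as the primary trial outcomes and adds: "Other pre- and postservice outcomes, such as proportion screened and time to screening, will also be evaluated". The cascade list under the heading Primary Outcome Measures also contains the proportions screened, assessed and in need, and the days to each. Table 1 defines the screened step as clinic referrals that have a screening date, without requiring the date to follow randomisation. The study-measures textbox expresses these identification steps as a "percentage of court cohort aged 12-17 years".

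**Analysis.** Cascade Outcomes states: "GLMM analyses of dichotomous outcomes (screening, treatment initiation, etc) will include intervention (FCFN group vs control group) as a fixed between-participants effect". Cox regression "will be used to compare the interventions on time-to-event outcomes (eg, time to assessment").

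**The concern.** A randomised comparison tells us about the intervention only through events that can still happen after allocation. A youth who is recruited while attending for screening, completes baseline and is then randomised will normally have a screening date on or before the randomisation date. Under the Table 1 definition that youth counts as screened whichever arm is drawn. Youth with existing petitions may also have been assessed, or found to be in need, before entry.

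For these youth any arm difference in screening status or days to screening is chance. Two misreadings are then possible. A chance imbalance could be taken as an effect of the navigator, or a near-null result forced by the design could be taken as evidence that navigation does not help early in the cascade. This matters because the pilot is meant to show preliminary impact along the cascade, screening included, and to inform a larger trial.

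The denominator adds a smaller difficulty. Neither the court cohort in the textbox nor the clinic referrals in Table 1 is the set of 80 randomised youth to which an arm comparison must apply.

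**Working it through.** **Order of events.** The article gives no sample-size calculation or effect size for screening, so there is no stated figure to reproduce. The check starts from sequence.

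1. Recruitment and Consent: contact may occur at the screening visit.
2. Randomization: allocation follows consent and baseline.
3. Eligibility: already-screened youth may enter.
4. Table 1: any screening date counts.
5. Cascade Outcomes: screening is modelled by arm.

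Taken together, these let events from before allocation into a between-arm comparison. Study Design puts study referral earlier, so the share affected is unknown.

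**Effect on the proportion screened.** Let s be the share already screened at randomisation, taken as equal in both arms, and let pC and pT be the later screening probabilities among the rest.

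- Observed rates: s + (1 − s)·pC and s + (1 − s)·pT
- Observed difference: (1 − s)·(pT − pC)
- Youth per arm who can still have the event: 40·(1 − s)

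**Illustration.** Assumptions: 40 per arm (from the protocol), two-sided alpha 0.05, pC = 69% and pT = 89%. The 69% borrows the local 6-month figure in the Background, which is for assessment and not screening; the 20-point gain is assumed. With Δ the difference, p̄ the mean of the two rates and n per arm,

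power = Φ{[Δ − 1.96·√(2p̄(1 − p̄)/n)] / √([pC(1 − pC) + pT(1 − pT)]/n)}.

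At s = 0.50 the observed rates are 84.5% and 94.5%, so Δ = 0.10 and p̄ = 0.895. The two standard errors are √(2 × 0.895 × 0.105/40) = 0.0686 and √((0.1310 + 0.0520)/40) = 0.0676. Power = Φ[(0.10 − 0.134)/0.0676] = Φ(−0.51) = 0.31.

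The last column applies the same formula with rates 69% and 89% and n = 40(1 − s), that is, restricted to youth not yet screened.

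| s | Observed rates | Difference | Able to change, per arm | Power, all 40 per arm | Power, restricted |
|---|---|---|---|---|---|
| 0 | 69.0% vs 89.0% | 20 points | 40 | 0.60 | 0.60 |
| 0.25 | 76.8% vs 91.8% | 15 points | 30 | 0.45 | 0.48 |
| 0.50 | 84.5% vs 94.5% | 10 points | 20 | 0.31 | 0.34 |
| 0.75 | 92.3% vs 97.3% | 5 points | 10 | 0.17 | 0.19 |
| 0.90 | 96.9% vs 98.9% | 2 points | 4 | 0.09 | 0.10 |
| 1 | 100% vs 100% | 0 | 0 | not estimable | not estimable |

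Other assumed rates show the same pattern. With all 40 per arm and s = 0, 0.50, 0.75 and 0.90, power is 0.79, 0.39, 0.20 and 0.10 for 45% vs 75%, and 0.87, 0.53, 0.29 and 0.14 for 69% vs 95%.

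Restriction therefore restores the size of the estimated effect but recovers little power: the information is lost when youth arrive already screened. The normal approximation is rough in the rows with few youth.

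**Time to screening.** On a clock started at randomisation, a youth screened earlier is never at risk. On a clock started earlier, that youth contributes an event time the intervention could not have influenced.

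**The case against.** The strongest reply is that the screening visit is only an example of a clinic contact, and that Study Design places study referral at the point of clinic referral, usually before screening. That stands. A reader might infer that the screening outcomes largely precede the intervention, or that at least half of youth are screened first. The article supports neither, and s could be near zero.

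A reader might also infer that the Cox models count days from referral and so carry pre-randomisation time into every cascade step. No time origin is stated, and the Cox example is time to assessment, not to screening. The full protocol or analysis plan may fix the origin, so its absence is no fault here.

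It is also fair to say that pre-allocation events balance between arms in expectation, so the harm is dilution and noise, not systematic bias. The hypothesis concerns only treatment initiation and engagement. The baseline record extract lets events before and after baseline be told apart, and Table 1 removes youth already in treatment from the referral count.

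What these replies leave standing is that the planned comparison includes screening by arm, that nothing described limits it to youth who could still be screened, and that the two recruitment statements point to different moments. The court-cohort denominator is a separate wording matter and is no evidence about timing.

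**Conclusion.** The point holds in a limited form. As written, the plan allows screening, and for some youth assessment and determination of need, to be compared between arms although the event came before allocation. Any true effect on the proportion screened shrinks by the factor (1 − s); at s = 1 both arms are 40/40 and no odds ratio can be estimated. The documents do not give s, so the range is 0 to 100%. The power figures rest on assumed rates and an assumed alpha and show direction only.

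The screening items sit under the heading Primary Outcome Measures, and a reader might conclude that the trial's main test is compromised. It is not: the abstract, Study Objectives and Hypotheses all name treatment initiation and engagement, which are unaffected. The change is worth making because it costs little and protects the cascade results that a larger trial would build on.

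**What to change.** 1. Reconcile Study Design with Recruitment and Consent, so that one point of recruitment relative to screening is stated.
2. Use the baseline record extract already planned for both arms under Assessment Data Collection to classify each youth by the steps reached at randomisation. Limit the between-arm comparisons of screening, assessment and need to youth who had not reached that step, and count time from randomisation. Because the restriction uses status before allocation, it keeps the randomised comparison intact.
3. Report steps completed before randomisation descriptively, by arm. If nearly all youth are screened beforehand, report proportion screened and time to screening only descriptively. Dropping the screening comparison outright would go too far while Study Design leaves room for randomisation before screening.
4. For arm comparisons, replace the court cohort as denominator with randomised youth, restricted as in step 2.

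The cost is wording and one derived variable, with no new data. The price is fewer youth in the two secondary screening comparisons, or their loss if s is close to 1, and smaller numbers for assessment and need where existing cases enter.

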#### Randomization

Participants will be randomized (using a computer-generated randomization tool) to either the FCFN intervention group (40/80, 50%) or the standard of care group (40/80, 50%) directly after consent and completion of the baseline assessment.

### Ethics Approval

This study was approved by the institutional review board at the University of California San Francisco (268565) and was conducted in accordance with the ethical standards of the Helsinki Declaration.

### Assessment Data Collection

Multiple sources of data will be collected, including electronic medical records (EMRs); mobile phone or web entry in the Fostering Connections web application; and self-reports from the FCFNs, youth, and caregivers (Textbox 1). Cascade mental health services–level data will be extracted from EMRs at baseline and at 1, 3, and 6 months for participants in both conditions. Assessments will be conducted via mobile phone or tablet device, depending on participant preference.

Study measures.
**Identification (percentage of court cohort aged 12-17 years; electronic medical record [EMR])**
Percentage screened (Child and Adolescent Needs and Strengths [CANS; short form]), percentage assessed (CANS), and percentage in needTime to screening, full assessment, and determination of need (number of days)
**Transition (percentage of those identified as in need; EMR)**
Percentage referred for treatment and percentage who initiated treatmentTime to referral and initiation (number of days)
**Retention (percentage of those referred for treatment; EMR)**
Engaged in care (≥6 weeks of attendance)Continuing care (number of total sessions completed)
**Navigator background (foster care family navigator [FCFN])**
Age, race and ethnicity, education, training, and years in child welfare field
**Number and types of contacts with navigator (Chorus platform, FCFN, youth, and caregivers)**
Video, SMS text messaging, in person, and telephone
**FCFN intervention fidelity (FCFN)**
Developed as part of prior study procedures
**Therapeutic Working Alliance (youth)**
Twelve-item Working Alliance Inventory [39], used in the Cannabis Youth Treatment Study [40], that assesses youth’s perception of therapeutic alliance over time
**Navigation Satisfaction Tool, Part I [41] (youth and caregivers)**
Twelve items that address client satisfaction with navigation services (eg, How satisfied are you with the navigator’s ability to listen and understand your concerns? How satisfied are you with the frequency of contact with the navigator?)
**Evidence-Based Practice Attitude Scale-50 (FCFN)**
A 50-item scale [42], developed and validated with mental health service providers, that assesses global attitudes toward the adoption of evidence-based practices
**Barriers to Care Questionnaire**
**(youth and caregivers)**
A 39-item scale (subscales of skills, marginalization, stigma, expectations, knowledge and beliefs, and pragmatics) [43] that assesses perceived barriers to child health care access; items are rated on the extent of the problem (ranging from 100 for “no problem” to 0 for “very big problem”), with higher scores indicating fewer barriers (items are at 5.7 grade reading level)
**Motivation for Youth’s Treatment**
**Scale**
**(youth and caregivers)**
A psychometrically valid 8-item scale [44] that youth and caregivers complete to measure intrinsic treatment motivation with the subscales of problem recognition and treatment readiness
**Mobile health (mHealth) feasibility or satisfaction (Chorus platform, youth, and caregivers)**
Mobile phone type, mobile phone service interruptions, number of mobile phone numbers, most preferred types of SMS text messages, number of messages opened or read, and responses
**Usability of mHealth intervention components or “system”: System Usability Scale (SUS; FCFN, youth, and caregivers)**
A 10-item measure [45] widely used to evaluate web applications that has proven superior to other measures; the SUS yields a single number representing a composite measure of the overall usability of the system being studied, and scores will be compared with established norms for levels of usability; our goal is a score of 80 (top 10% of scores), which reflects excellent usability and is associated with recommending the product to a friend
